## 1.2. Investigational food supplements

Twelve investigational food supplements will be developed based on current available evidence (*[name] KF et al, 2009; Golden M, 2008*) and international guidance (WFP, WHO, MSF, ALIMA). These include improved CSB based supplements (iCSBS) and LNS combining different soy qualities and different amounts of total protein provided by dry skimmed milk (DSM), as follows:

- 3 iCSBS based on dehulled soy, with either 0%, 20% or 50% of total proteins provided by DSM
- 3 iCSBS based on soy isolate, with either 0%, 20% or 50% of total proteins provided by DSM
- 3 LNS based on dehulled soy, with either 0%, 20% or 50% of total proteins provided by DSM
- 3 LNS based on soy isolate, with either 0%, 20% or 50% of total proteins provided by DSM

Thus a total of 12 products, 6 in the form of LNS and 6 in the form of CSB.

---

 0%, 20% and 50% of total protein provided by DSM corresponds to 0%, 8% and 20% of total weight.

Both types of product will comply with the WHO technical note “Supplementary foods for the management of moderate acute malnutrition in infants and children 6 – 59 months of age”(WHO 2012)

The products will not have the same nutrient density per 100g, but will provide the same total amount of protein and micronutrients per daily serve (130g of CSB or 92g of LNS).

The fatty acid profile will be similar in all twelve products and the same supplier for the main raw material, dehulled soya and soy isolate, will be used for both LNS and CSBs.

A vitamin and mineral premix will be designed for all products and will meet the quantities specified in the WHO technical note. Some adjustments will be necessary between products because e.g. dry skim milk in larger quantities will be a significant contributor of e.g. calcium, potassium and phosphorous, and because the concentration of certain vitamins decreases during the preparation of CSB. The aim is a uniform micronutrient composition across all products for final consumption.

For a detailed description of the composition of the products, please see annex 2.

LNS will be provided in individual packaging, ready for consumption with no need for preparation or cooking. All LNS individual packs will have similar packaging, whatever the type of soy or the milk content, and will only differ by a number.

iCSBs fortnightly food rations will be delivered to the caretakers in bags of 1.7 kg which corresponds to a bi-weekly ration (130 g/child/day). All iCSB bags will have similar packaging, whatever the type of soy or the milk content, and will only differ by a number. iCSBs have to be consumed as a porridge or gruel. The flour should be mixed with an appropriate proportion of clean water followed by a cooking time at simmering point from five to maximum ten minutes.

For children with MAM, it is usually recommended to provide a food supplement daily ration of 75 kcal/kg that covers the daily micronutrients requirements (*Manary et al, 2008*). In addition to the usual diet, this quantity is sufficient to promote catch up growth. However, in order for possible intra-household food sharing to be taken into account, many organizations usually distribute a food supplement providing at least 1000 kcal/day, which appears relatively high for children with MAM (*[name] S et al, 2009*). Children with MAM (weight-for-height  $\geq -3$  and  $< -2$  Z-scores ) and measuring between 65 and 87 cm are expected to weigh between 5.5 and 10.4 kg (WHO growth standard). These children would therefore need a food supplement daily ration of 413 kcal (5.5 kg \* 75 kcal/kg) to 780 kcal (10.4 kg \* 75

kcal/kg). In this study, children will receive a fixed daily ration equivalent to 500 kcal/day. The same amount of energy will be provided for all food supplements.

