### *3.1.3. Interventions: food products and quantities, medical treatment and incentives*

#### **Food products and quantities**

Children will receive 500 kcal/day. Food will be distributed fortnightly during a 3 month period. At each visit, a ration will be given on the spot. Mothers will be asked to bring back the empty LNS packs at the next visit to give to the personnel charge of the supplement (not to staff involved in measurements, to ensure blinding).

CSB will be provided in bi-weekly rations, to be prepared at home.

During the entire follow-up, any child developing severe acute malnutrition (WHZ less than – 3 z-scores, MUAC <115 mm or edema) would be referred for treatment of SAM. The following children will be referred to Yako pediatric unit, which is supported by ALIMA, for medical evaluation;

- Children admitted based on WHZ  $\geq$  -3 - and < -2 z-scores who have not reached a WHZ  $\geq$  -2 z-scores at the end of the 3 months intervention
- Children admitted on MUAC  $\geq$  115mm and < 125 mm who have not reached 15% weight gain,
- Children presenting a weight loss  $\geq$  5% from his/her weight at baseline for two consecutive visits.

Should these children receive other nutritional intervention during their hospitalization, they will be withdrawn from the study as failures to respond to treatment. Data obtained after receiving other nutritional intervention than previewed will not be included for data analysis.

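### The 1.7 kg iCSB bag does not equal a fortnight at 130 g/day (1.82 kg); the resulting shortfall is 0% to 6.6%, depending on an ambiguous sentence about the ration given at visits

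*Combined protocol and SAP*

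**What the plan says.** Section 1.2 (Investigational food supplements) fixes the quantities. The products "will provide the same total amount of protein and micronutrients per daily serve (130g of CSB or 92g of LNS"). On energy it says "In this study, children will receive a fixed daily ration equivalent to 500 kcal/day", and then "The same amount of energy will be provided for all food supplements". For packaging, iCSB comes "in bags of 1.7 kg which corresponds to a bi-weekly ration (130 g/child/day"), and the same sentence calls these fortnightly rations. LNS is described only as individually packed and ready to eat. Neither the pack size nor the number of packs per fortnight appears in the text available.

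Section 3.1.3 (Food products and quantities) sets the handing-out: "Food will be distributed fortnightly during a 3 month period". It adds "At each visit, a ration will be given on the spot", and, after a sentence on the return of empty LNS packs, "CSB will be provided in bi-weekly rations, to be prepared at home".

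Section 3.1.13 puts both product types into one three-way model for the change in lean body mass, with pairwise comparisons within and across the two types.

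**The concern.** The bag weight, the daily serve and the interval are all stated, and they do not fit together. This matters because the same section promises equal energy, protein and micronutrients per day from all twelve foods.

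If less iCSB than LNS were supplied, the deficit would fall on six of the twelve cells, 6 × 134 = 804 of 1,608 children, and would line up exactly with the product-type factor. Randomization could not separate the two, because the deficit would be part of the allocated treatment. The planned covariates (baseline lean mass, age, sex, MUAC, WHZ, season, centre) could not do so either. A difference in quantity supplied could then be read as a difference between product types.

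**Working it through.** **Inputs.** Bag 1,700 g, iCSB serve 130 g/day and energy 500 kcal/day, all from section 1.2; interval 14 days, from section 3.1.3. I assume that the 130 g serve carries the 500 kcal, which is how section 1.2 presents them. The annex with the compositions is not in the text available.

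**Step 1: try to reproduce the 1.7 kg.** Days × 130 g:

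- 12 days: 1,560 g
- 13 days: 1,690 g
- 14 days: 1,820 g
- 15 days: 1,950 g

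The stated fortnight does not give 1.7 kg; 13 days does, to within 0.6%. Conversely, 1,700 / 130 = 13.1 days. Rounding does not explain the gap: a bag of 1.75 kg, the most that could be printed as 1.7, is still 1 − 1.75/1.82 = 3.8% short. Nor can bi-weekly mean twice a week, since the bag holds about 13 daily serves.

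**Step 2: the bag is the only supply for 14 days.**

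- Shortfall: 1,820 − 1,700 = 120 g; 120 / 1,820 = 6.6%
- Daily amount: 1,700 / 14 = 121.4 g
- Daily energy: 500 × 121.4 / 130 = 467 kcal, or 33 kcal below 500
- Over six fortnights: 6 × 120 = 720 g; 720 × 500 / 130 ≈ 2,770 kcal per child

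Protein and micronutrients fall in the same proportion.

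**Step 3: one separate 130 g serve is also given at each visit.**

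- Daily amount: (1,700 + 130) / 14 = 130.7 g
- Daily energy: 500 × 130.7 / 130 = 503 kcal, so no shortfall

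**Step 4: which reading does the text support?** Neither decisively.

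- For step 3: 13 home days reproduce the bag weight. Section 3.1.3 mentions the on-the-spot ration and the home-prepared iCSB ration in separate sentences. Section 3.1.5 has the first dose eaten under observation, so some product is consumed on site.
- For step 2: section 1.2 equates the bag with the fortnight's ration, not with 13 days. The on-the-spot sentence is followed directly by the return of empty LNS packs at the following visit, which suggests handing over the take-home supply. Section 1.2 requires iCSB to be simmered, and no visible section describes cooking it at routine visits. Supervised eating is described for the first dose only.

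**Step 5: the comparison with LNS.** Bias needs a difference between product types, and only the iCSB side can be calculated. If the bag is the sole iCSB supply and LNS covers 14 full days, the difference is 33 kcal/day. If both types cover 13 days at home and one on site, there is essentially none.

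**The case against.** The strongest reply is that the bag weight is deliberate: 13 days at home plus one serve at the visit, 1.69 kg printed as 1.7 kg. This fits the arithmetic well and the documents do not rule it out. It stands as a live possibility and is why the lower end of the range is 0%. It does not rescue the sentence in section 1.2, because on that reading the bag is a 13-day supply and not the fortnight's ration.

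A reader might go further and infer that the iCSB half of the trial does receive 6.6% less energy, and that the LNS-versus-iCSB result is therefore biased against iCSB. The documents do not support that. The shortfall depends on a sentence that can be read two ways. It is also tempting to assume that LNS comes in daily packs with no deficit, but section 1.2 says only that packs are individual.

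Three further points limit the reach, and all stand:

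- All six iCSB foods share the same stated bag and serve, so the soy and milk contrasts made within iCSB are not touched.
- Grams supplied are not grams eaten. Section 1.2 raises sharing within the household, and section 3.1.14 names poor adherence as a possible limitation and frames the trial as one of effectiveness.
- Section 3.1.11 collects quantities consumed through the visit questionnaire, so a real difference in intake would be at least partly visible.

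None of these says what was meant to be supplied, which is the open question.

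**Conclusion.** The inconsistency is certain: 1.7 kg is not 14 × 130 g, and the gap is 120 g per fortnight. Its effect on the energy supplied is not certain. Taking 1.7 kg at face value and 130 g as 500 kcal, the iCSB shortfall is 6.6% (467 kcal/day) if the bag is the only supply, and 0% (503 kcal/day) if one 130 g serve is added at each visit. The roughly 2,770 kcal per child over the intervention is the upper end and not an estimate.

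Bias in the LNS-versus-iCSB contrast is conditional on LNS supply per fortnight being different in energy, which the visible text does not allow anyone to check. The sample size and the within-iCSB contrasts are unaffected. The point is worth correcting because it concerns how much of the intervention is delivered and bears on one of the three factors of the primary model.

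**What to change.** Before packing, reconcile the daily serve and the bag weight in section 1.2 with the distribution text in section 3.1.3, and correct whichever figure or sentence is wrong. For iCSB and LNS alike, state:

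- grams (and, for LNS, packs) handed out per fortnight;
- the number of days this is meant to cover;
- whether the ration given at the visit is additional to the take-home supply or counted within it.

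The stated supply should then be checked against the equal-energy statement in section 1.2. This review takes no view on which ration is right.

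If bags are already packed, record the amount supplied per child and report the LNS-versus-iCSB result alongside the energy actually supplied in each product type. The cost is a corrected figure or sentence and a supply check with the manufacturer; no change to design, sample size or analysis model is needed.

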### 1.3. Outcomes measures

Previous studies have often assessed the effect of various foods supplements for MAM on so-called "*nutritional recovery*", i.e. increments in the weight-for-height indicator to above a certain value (*Nackers F et al, 2010; Matilsky DK et al, 2009; Ciliberto MA et al, 2005; Patel MP et al, 2005*). However, weight gain alone is a suboptimal indicator, as it may merely reflect accumulation of fat and therefore not a long-term benefit for the child. When assessing child nutritional improvement, standard anthropometric measurements, i.e. weight, height, mid-upper-arm circumference (MUAC), and kneeheel length, as a measure of short-term linear growth (*Doherty et al, 2002; [name] KF 1997*), should be taken into consideration. Furthermore, additional indicators are needed to better assess the quality of the recovery.

An important indicator is body composition, namely what components comprises a person's body weight. In the most simple body composition model, body weight is divided in fat-free and fat-body mass (*International Atomic Energy Agency (IAEA)*). Fat free mass or Lean Body Mass (LBM) is known to be associated with survival in starvation and acute illness (*Sauerwein HP et al, 2010*) and to be accompanied by beneficial functional outcomes (*Wells J et al, 2009, Roubenoff R et al, 1991*). Several methods allow for the assessment of body composition, although there is no gold standard in vivo. Some of these techniques (such as dual-energy x-ray absorptiometry, or densitometry by plethysmography) require specialized equipment and do not appear suitable for conducting research in children living in developing countries. One easy-to-use technique is the measurement of the skin fold thickness (of the arm and/or the trunk) as an estimation of subcutaneous fat depots. This has been used for decades (*Wells J et al, 2008*) and tables of "triceps and sub scapular skinfold-for-age z-scores" are included in the new WHO Child Growth Standards (*WHO 2007*). The ratio between the triceps and the sub scapular skin folds allows describing the relation between central and peripheral fat depots. However, skin-fold thickness does not provide direct information on the LBM and it suffers from low intra- and inter-observer reliability (*Wells JC et al, 2006*).

It is therefore reasonable to use a second technique, LBM can also be assessed indirectly by measuring the total body water of a child. The total body water can be measured using a

---

 Water is the largest component of the body and is found exclusively in the fat free mass. Total body water includes both intracellular fluid and extra cellular fluid.

tracer consisting of heavy water (deuterium oxide,  $^2\text{H}_2\text{O}$  or  $\text{D}_2\text{O}$ ). This tracer is naturally occurring in body water in small amounts, and total body water is assessed by measuring the concentration of the tracer in saliva samples from a child taken before and after oral administration of the tracer. With the estimation of total body water it is possible to estimate the amount of LBM from the hydration of fat free mass (IAEA). The tracer technique is regularly used in human studies in both developed and developing countries, including West African countries such as Senegal (Dioum et al, 2005; Diouf et al, 2009) and appears to be appropriate for use in infants and young children (Wells JC et al, 2006, IAEA). The University of Copenhagen has recent experience using this technique in developing countries such as Tanzania, Ethiopia and Cambodia (Praygod G, 2013 and other yet unpublished studies).

Beneficial functional outcomes linked to nutritional status also include immune function, physical activity and child development. The immunodeficiency associated with malnutrition is the primary reason for children with malnutrition to be more susceptible to infectious disease, and more likely to die than their well-nourished peers. The nature of this immunodeficiency is only partly understood, but it is well established, that the size of a child's thymus is a useful indicator of the "immunodeficiency of malnutrition" (Savino and Dardenne, 2010). Malnourished children have small thymuses, and studies from West Africa have found a small thymus is a strong and independent risk factor for mortality (Garly et al, 2008; Aaby et al 2002). The size of the thymus can be assessed by ultrasound (Jeppesen 2003).

The level of physical activity may be an indicator of wellbeing in children and changes may affect body composition (Reichert et al 2009). Thus, associations between physical activity, weight change and changes in body composition during nutritional rehabilitation are important to evaluate. This can be assessed using an accelerometer (Cliff DP et al, 2009). Further, malnutrition may also alter cognitive development (Victoria 2008) and delay the achievement of motor and cognitive milestones of young children. This can be measured with a child development test such as the Malawi Developmental Assessment Tool (MDAT) recently validated in Malawi (Gladstone et al, 2010)).

In addition to anthropometric, LBM and functional outcome measures, biological indicators may also help assess changes in nutritional status. Blood hemoglobin and serum ferritin levels are used to evaluate the effect of nutritional interventions on anemia and iron status respectively (Lopriore C et al, 2004; Kuusipalo H et al, 2006; Andang'o PE et al, 2007).

In addition, nutritional status plays an important role in the regulation of the serum insulin-like growth factor-1 (IGF-1) and its variations may serve to monitor improvement in children's

---

 The method is a state-of-the-art method adapted to field use and recommended by the International Atomic Energy Agency (IAEA) in Vienna, Austria.

nutritional status, particularly in relation to linear growth (*Kouanda et al, 2009*). Since, the acute or chronic inflammatory status might influence the levels of ferritin (*Beard et al, 2006*) and IGF-1 (*Kouanda et al, 2009*), it is recommended to measure, simultaneously, serum concentrations of acute phase proteins (APP) such as slow reacting  $\alpha_1$ -acid-glycoprotein (AGP) and the C-reacting protein (CRP). These APP are also objective markers of infections and have been shown associated with maternal reports of morbidity among Ghanian (*Filteau SM et al, 1993*) and Zambian (*Filteau SM, unpublished observations*) children.

Finally, essential fatty acids (EFA) are crucial for child growth and development (*Uauy et al, 2003*) and malnourished children may be EFA-deficient (*Squali Houssaïni FZ et al, 2001; Decsi T et al, 1998; Briend et al, 2011*). Blood EFA levels can be used to assess the impact of dietary interventions on fatty acid status (*Fratesi et al, 2009; Briend et al, 2011*) and might therefore help evaluating child nutritional rehabilitation in this trial.

#### 1.4. The context of Burkina Faso

Burkina Faso has approximately 17 million inhabitants. Child mortality in the country is high, with an average of 176 deaths per 1000 live birth in children less than 5 years old. The high child mortality rate is among other things due to malnutrition (*Black RE et al, 2008*).

According to a recent SMART survey carried out in August-September 2011 (*Ministère de la Santé and Direction de la Nutrition, Burkina Faso, 2011*), the prevalence of Global Acute Malnutrition in Burkina Faso is 10,2% (95% CI 9,6-10,7%), which is high if compared to the 10% emergency threshold as defined by WHO.

Similarly to other countries in the Sahel region, Burkina Faso is affected by recurrent food insecurity and nutrition crisis. This was last seen in 2012 where late rains, reduced harvest and increased food prices (by 30-60% between January 2011 and January 2012) and left the population more vulnerable and prone to malnutrition.

The treatFOOD project will take place in the Province du Passoré also known as the health district of Yako (after the main city). It is part of the northern region together with the districts of Gourcy, Séguénéga, Titao et Ouahigouya and consists of 9 departments: Arbolé, Bagaré, Bokin, Gomponsom, Kirsi, Latoden, Pilimpikou, Samba et Yako.

The province covers an area of 4078 Km^2 and has 372 403 inhabitants including 70 017 children under 5 (Ministère de la Santé, District Sanitaire de Yako, 2011). The main city of Yako is about 110 Km from the country's capital Ouagadougou.

The district of Yako has 53 health centres and 1 small hospital. Each village has two agents de santé communautaires (community health workers) who support the health staff with some aspects of their work such as community sensibilisation and mobilization as well as health education.

In 2011 the malnutrition rates in the province were 11.8% (GAM) and 1.6% (SAM) and one of the areas identified to be at risk of food insecurity and a priority region for WFP.

From 2007-2011 the management of malnutrition in the province was ensured by Médecins sans Frontiers-France (MSF-F), who handed over their activities to the Ministry of Health in July 2011. Since July 2012, the NGO ALIMA has in collaboration with a local NGO KEOOGO been implementing a nutrition program in the same area in the province where MSF-F was previously working. The objective of the program is to support government health structures in the treatment of SAM.

ALIMA is working together with KEEOGO in supporting the 53 health structures in the district for diagnosis and outpatient treatment of SAM. ALIMA is furthermore supporting the in-

patient treatment of SAM at the paediatric unit at Yako hospital by reinforcing capacity and providing technical support. For more information on ALIMA and KEOOGO, please see annexes 3 and 4.

Recruitment and follow-up of children enrolled in the research project is planned to take place in five CSPS supported by ALIMA. In many of the CSPS, un-used structures from when MSF-F used to support activities, are present and could be used for the project, if adjusted and renovated slightly. Behind the research project is an experienced research team who will take turns being based in Yako for supervision and support. Furthermore local staff will be recruited and trained for the implementation of the research project, in addition to existing health staff at the CSPS.

## 1.5. Rationale

Nutrition is one of the main socio-economic and political issues of Burkina Faso and is a priority for the government in order for the Millenium Development Goals to be reached. The treatment of SAM has improved significantly in recent year while guidelines for the treatment of MAM have remained unchanged. In many countries including Burkina Faso, although guidelines here are in the process of being changed, treatment with CSB is still recommended for the management of MAM. However, CSB has been proven to be inadequate for the treatment of malnutrition in children due to among other things high levels of anti-nutrients, inadequate micronutrient and protein content as well as a high viscosity (*[name] et al, 2009*).

Treatment of MAM is essential in a public health perspective and in some of the most affected regions in Burkina Faso, aid organizations are currently introducing improved CSBs (CSB+ and CSB++) and other products for the management of MAM, including lipid based nutrient supplements. However, there is no consensus on how to manage children suffering from MAM and which the best product is. New food products should be tested using outcome measures of importance for body function, rather than just increase in weight. Randomized trials with lean body mass as the primary outcome and functional measures as secondary outcomes are needed to identify new cost-effective food supplements for MAM management. In this respect, the present proposal aims at comparing the effectiveness of improved diets in the nutritional improvement of children with MAM in Burkina Faso, considering the cost of the experimental food supplements.

